### Optional HIV and STI Testing

Biological specimens are collected for HIV and/or bacterial STI testing from relevant anatomical sites of participants who have clinical indications, as determined by their medical provider. Participants for whom HIV and/or STI testing are not clinically indicated but who request and consent to the optional additional cohort testing have a flag added to their patient chart by research staff, alerting the provider to order these tests. All specimens are sent to the clinics’ site labs for analysis, per medical department procedures. Participants complete these tests in concert with their routine lab work. Test results are extracted from their patient chart.

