The electronic informed consent form (eICF) for the survey is programmed into REDCap (Research Electronic Data Capture) and is the second form of the electronic survey, preceded only by an eligibility confirmation form. The eICF describes and addresses all study procedures, including confidentiality and privacy, information about potential risks, discomforts and benefits of participation, and information regarding members of the research team to contact for further questions. It also states that participation is voluntary, that participants may decide not to take part or withdraw from the study at any time without penalty or loss of any benefits to which they might otherwise be entitled, and that study participation is in no way related to being able to access or continue receiving care or services at Fenway Health or Callen-Lorde. Participants are provided with contact information for study staff and are encouraged to call or speak with a staff member if they have any questions before consenting. If a participant agrees to join the study voluntarily, they are asked to consent to the following by checking the applicable boxes: (1) the survey, (2) optional HIV testing, and (3) optional STI testing. Participants who do not consent to optional HIV and/or STI testing are still provided the option to complete the survey.

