### Statistical Considerations

The study outcomes are viral suppression (for TGD patients living with HIV); PrEP uptake (for TGD patients not living with HIV); and incident syphilis, gonorrhea, and chlamydia diagnoses by anatomical site (for all patients, irrespective of HIV status). The primary exposure is medical gender affirmation (hormones and surgery).

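### STI diagnosis is compared in all patients, but testing follows indication or request, so the comparison can mix infection risk with detection if testing differs by exposure

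*Protocol article*

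**What the plan says.** Statistical Considerations defines the STI outcome as incident syphilis, gonorrhea and chlamydia "diagnoses by anatomical site (for all patients, irrespective of HIV status"), and states: "The primary exposure is medical gender affirmation (hormones and surgery"). Table 1 also lists STI diagnosis in all patients (there chlamydia and gonorrhea) as a primary outcome, with patient survey, EHR and laboratory as its sources.

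Optional HIV and STI Testing describes how infections come to light. Specimens are taken "from relevant anatomical sites of participants who have clinical indications, as determined by their medical provider". Patients without an indication "who request and consent to the optional additional cohort testing have a flag added to their patient chart", which prompts the provider to order the tests. On timing: "Participants complete these tests in concert with their routine lab work". On the source: "Test results are extracted from their patient chart". Consent to optional testing is given inside the survey and can be refused: "Participants who do not consent to optional HIV and/or STI testing are still provided the option to complete the survey".

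Data Analysis plans generalized estimating equations adjusted for individual, interpersonal and structural covariates. Table 1 itemises those domains. Mental health care and medication utilization is the nearest entry to contact with services; STI testing and visit frequency do not appear. The missing-data paragraph plans a review of missingness patterns and multiple imputation as appropriate, and separately a sensitivity analysis for unmeasured confounding. Limitations names self-selection into hormones and clinic patient bias, but not differential testing.

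**The concern.** A diagnosis in the chart needs both an infection and a test. Here the test depends on the provider's judgement, the patient's request and the occasion of routine lab work, and each of these can be related to receiving hormones or surgery. The article gives a reason to expect such a relation. Its Rationale proposes that delivering gender affirmation in primary care may increase engagement with HIV prevention and care services, and its conceptual framework says that meeting this need frees patients to attend to HIV prevention and treatment. If that is right, exposed patients may be tested more often, and part of the intended benefit would appear as a higher diagnosis rate.

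At stake is what an exposure coefficient for this outcome means. It could suggest harm where infection risk is equal, or hide a real reduction.

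**Working it through.** **1. The plan's own figure.** Tables 2 and 3 give P0 = 0.052, P1 = 0.210, 47 unexposed and 213 exposed, 260 in total. The pooled two-sided normal formula at alpha 0.05 and 80% power, with allocation ratio 213/47 = 4.53, returns 47 unexposed. Power at 47 and 213 is 80.2%. The arithmetic reproduces and is not at issue.

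**2. How uniform is testing?** By April 2020, 1756 of 7821 warehouse patients (22.5%) had a baseline survey. Consent to optional testing is part of that survey, so for the other 77.5% the only route described is routine care.

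**3. Formula.** Let q be the true infection risk, equal in both groups, and s1 and s0 the probabilities that an infected exposed or unexposed patient is tested. Assume near-perfect tests, and that an untested infection produces no diagnosis in the analysis. Then

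observed risk = q × s, and spurious RR = (q × s1)/(q × s0) = s1/s0.

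The relevant share is P(tested | infected), not the overall share tested. The two coincide only if testing is unrelated to infection within each group.

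**4. Values.** The documents give no testing share by exposure, so all of these are assumed:

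| Scenario | s1 | s0 | Spurious RR |
|---|---|---|---|
| Indication finds most infections | 0.95 | 0.85 | 1.12 |
| Testing unrelated to infection | 0.80 | 0.60 | 1.33 |
| Testing unrelated to infection, wider gap | 0.90 | 0.60 | 1.50 |

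A real benefit can also be hidden: true RR 0.75 × 1.33 = 1.00 observed. If s1 is smaller than s0, the distortion runs the other way.

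**5. Chance of a spurious p < 0.05.** Two-sided, unadjusted, using the current-hormone split in Table 4 (6855 v 966) and the planned split in Table 3 (213 v 47). The values of q are 0.21 and 0.052 from Table 2, and 0.10 as an intermediate assumption.

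| q | s1 v s0 | 6855 v 966 | 213 v 47 |
|---|---|---|---|
| 0.21 | 0.95 v 0.85 | 33% | 5% |
| 0.21 | 0.80 v 0.60 | 93% | 9% |
| 0.10 | 0.80 v 0.60 | 59% | 5% |
| 0.052 | 0.80 v 0.60 | 32% | 4% |

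The risk of a false signal is mainly in a full-warehouse analysis.

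**6. Would restricting to tested patients solve it?** Not by itself. Positivity among the tested is q × s/t, where t is the overall share tested. Take t = 0.90 and s = 0.95 in the exposed, and t = 0.60 and s = 0.85 in the unexposed (assumed). The ratio is (0.95/0.90)/(0.85/0.60) = 1.056/1.417 = 0.75. With equal true risk, exposure now looks protective, because the unexposed are tested more selectively.

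**The case against.** The strongest reply is that the article does not say how untested patients are coded. A reader might infer that they count as free of infection, since the outcome is a diagnosis in all patients. No section says so, and the missing-data paragraph would also allow untested intervals to be treated as missing. A condensed article may leave that coding to the full protocol or analysis plan. This stands: the coding is not a finding in itself.

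A reader might also infer that more testing in hormone patients will necessarily appear as more STIs. The documents do not support that. They give no visits, lab contacts or STI tests by hormone status, and the Rationale says only that engagement may rise. Table 5 shows 372 of 1756 (21.18%) never tested for an STI, and 95 + 95 = 190 (10.8%) unsure or missing. These are lifetime figures for the survey subset, not split by exposure, and say nothing about differential testing over 12 months.

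Nor can a risk ratio of 1.5 or more be read off overall testing shares. To the extent that indication-based testing finds the infections, the ratio moves towards 1, as the first scenario shows.

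It can also be said that Table 1 lists data domains rather than final model terms, that the survey asks about STI screening history, and that self-report may capture diagnoses made elsewhere. All true, but self-report also depends on a test somewhere and reaches only survey patients. What remains is an all-patient outcome, non-uniform testing and a stated expectation of higher engagement, without any described step that separates detection from infection.

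**Conclusion.** The concern holds in limited form. The all-patient STI comparison can mix infection risk with detection if testing differs by exposure, and the article's own framework makes a difference plausible. Direction and size are unknown from the documents. Under assumed testing shares with equal true risk, the spurious risk ratio runs from about 1.1 to 1.5. This assumes that exposed patients are tested more, that an untested infection is analysed as no diagnosis and, for the 1.3 and 1.5 figures, that testing is unrelated to infection. Coding untested intervals as missing would not remove the problem if the reason for testing is unmeasured. The all-patient outcome need not be abandoned; the point is a low-cost improvement that changes what may be concluded about STI risk.

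**What to change.** - Keep the all-patient diagnosis analysis, and label it detection-dependent.
- Report STI testing frequency by exposure group and anatomical site from the EHR.
- State how untested person-intervals are handled, and do not code them as STI-negative without a check.
- Add a prespecified analysis weighted by the inverse probability of testing, using EHR covariates, visit counts, PrEP status, and risk behavior or testing indication where recorded.
- Interpret an exposure effect on STI risk only if the two analyses agree; otherwise report a difference in diagnoses.
- Name differential testing under Limitations.

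The cost is analysis wording and some programming. Data Sources says that appointments, lab orders and results are already in the EHR systems feeding the warehouse. The weighted analysis has fewer informative intervals. It keeps residual bias in either direction if the reason for testing is not fully measured, including inflated positivity in a group tested mainly on indication. That is why it should stand beside the all-patient result and not replace it.

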### Study Retention

We expect to retain approximately 85% of those who consent to additional procedures (electronic survey and HIV or STI testing) across 12 months of follow-up. Data informatics personnel and research assistants at each site work collaboratively to track cohort participants and contact participants when it is time to take their follow-up surveys. Study activities are synced with routine clinical care as much as possible to minimize participant burden. Study retention and participant engagement activities are ongoing. Participants can opt-in to receive study updates in the form of a newsletter. Study updates occur via email approximately 3 times over 12 months. The email contains general updates about the study (eg, how many have enrolled to date, fun facts about the cohort, and other study milestones) and infographics with deidentified preliminary demographic and other data. The email is not sent to those who have declined to receive study updates. The purpose of the newsletter is to provide progress updates to participants and promote participant engagement, including evoking feelings of being *part of* and actively contributing to the project and the study team at each site. The newsletter emails are sent via a health insurance portability and accountability act (HIPAA)–compliant mass-messaging platform.

### LEGACY RDW Procedures

The LEGACY RDW is a HIPAA limited data set. The HIPAA limited data set may contain extensive clinical information on study participants but limits patient identifiers and other unique characteristics to preclude the possibility that the patient could be identified using data transmitted to the RDW.

### Quality Assurance

The LEGACY RDW employs various data resources to aid in the quality, maintenance, and security of patient data. Data resources are maintained, regularly monitored, evaluated, and updated. For survey data, quality assurance (QA) begins in the recruitment process. Recruitment scripts screen health record data to determine prospective patients’ eligibility before outreach. Research assistants review the outputs for these scripts and report any suspected ineligible patients so that necessary updates may be applied. Patients deemed eligible by the recruitment scripts are then offered a screener where they self-report eligibility criteria before the consent process. The survey uses restricted input options and pathing logic to promote data accuracy and completeness. In some cases, key survey data points are crosstabulated and reviewed for any erroneous response patterns not identified by the survey’s built-in QA tools. QA for the LEGACY RDW includes running scripts across data tables to check for errors, such as duplicated rows and orphaned records. The LEGACY RDW relies on the QA processes managed by the native EHR systems for measures of completeness and accuracy. Staff at both sites regularly maintain extraction, transformation, and loading scripts to ensure they are congruent with the most recent version of their native EHR systems.

### Data Sources

The LEGACY RDW integrates outpatient, health center, and patient self-reported survey data for TGD patients into a single data management system (Figure 2). The comprehensive EHR systems at Fenway Health (Centricity Practice Solutions, athenahealth product) and Callen-Lorde (NextGen Ambulatory EHR, version 5.9/8.4) include patient demographics; registration and appointments; claims; encounter or problem list diagnoses; vital signs; lab orders and results; prescriptions; procedure or referral orders; provider notes; PROs conducted as part of routine clinical care (eg, screening for smoking, depression, and violence); imaging services; behavioral health data; dental care data; and information on patients with acute, chronic, or episodic conditions requiring special attention. These comprehensive outpatient data sources capture information on a broad range of primary care services, the most common services used by US patients. These data sources also include specialty care services to inform research questions regarding medical gender affirmation, HIV prevention, and HIV care. The LEGACY RDW is designed to enhance the breadth of the horizontal outpatient data sets by adding vertical depth with self-reported survey data from patients. Integrating electronic patient-reported survey data allows gathering of information that is not currently captured in the patient record (eg, incarceration, desires for gender-affirming procedures, and experiences in health care) to achieve the main study aims.

**Figure 2 figure2:**
[figure not shown]
LEGACY cohort: study flow diagram. EHR: electronic health record.

### EHR Data Submission Procedures

A data usage agreement (DUA) was established before Callen-Lorde shares any identifying information regarding their patients with Fenway Health.

Data come directly from the partnering site. Partners have access to a secure FTP (file transfer protocol) server within Fenway Health’s firewall to transfer the limited data set. Data partners have their own user IDs and passwords, and each data partner’s data set is segregated into individual directories. A waiver of consent and authorization specifically for patient data coming from partners’ EHRs was granted because it is not practicable to go back and obtain consent and authorization from the over 5000 patients whose health records make up the RDW.

### LEGACY Surveys

Self-report survey data for TGD patients are collected using REDCap [70,71]. REDCap is a secure web-based app validated to ensure HIPAA-compliant data collection. Survey data collected through REDCap are stored on a secure Fenway Health server before being extracted and transferred into the LEGACY RDW. Consent obtained before survey administration is stored in REDCap, with survey data and transferred into the LEGACY RDW along with survey responses.

Although the survey is hosted on Fenway Health’s servers, each research site manages survey administration for their own patients. Patient email addresses are maintained within their REDCap study records to enable the emailing of surveys to patients. To permit Callen-Lorde staff to enter their patients’ email addresses into Fenway Health’s REDCap server, both parties signed a DUA that covers sharing Callen-Lorde’s patients’ email addresses with database administrators at Fenway Health. Callen-Lorde was given their own REDCap project and log-in credentials for managing their surveys. Database administrators at Fenway created REDCap user access groups that restricted other Fenway Health staff from accessing Callen-Lorde’s REDCap records and restricted Callen-Lorde staff from accessing Fenway Health REDCap records. Fenway Health database administrators are the only staff members with access to REDCap study records for both sites.

Fenway Health uses patient medical record numbers (MRNs) as the primary identifier for their patients’ REDCap study records. Patient MRNs are replaced with LEGACY study IDs before the survey data are imported into the LEGACY RDW. Callen-Lorde preassigns LEGACY study IDs to their patients and uses the study ID as the primary identifier in their patients’ REDCap study records. Callen-Lorde’s study staff maintains their own link file connecting their patients’ study records back to their MRNs outside of REDCap. Callen-Lorde’s patients’ MRNs are never entered into the REDCap study records.

### Security and Confidentiality

The LEGACY RDW is stored within Fenway Health’s secure firewall on a server requiring log-in credentials from authorized Fenway Health staff. Only the Fenway Health database administrators assigned to the project have direct access to the full RDW. All other study personnel who require access to any data elements are given access to the appropriate data elements according to their role and need. In preliminary steps, data structures are designed to separate personal identifiers from other critical data, further enhancing protection. All partnering organizations meet or exceed the requirements for patient data safety established in the federal HIPAA guidelines.

### Confidentiality Agreements

All persons employed by Fenway Health and Callen-Lorde sign a confidentiality agreement. Fenway Health has an excellent record of using EHR data for research without breach of confidentiality. No individual-identifying data will be published or released, and data will be summarized and presented in public forums only as aggregate measures or as results from statistical analyses.

### Statistical Considerations

The study outcomes are viral suppression (for TGD patients living with HIV); PrEP uptake (for TGD patients not living with HIV); and incident syphilis, gonorrhea, and chlamydia diagnoses by anatomical site (for all patients, irrespective of HIV status). The primary exposure is medical gender affirmation (hormones and surgery).

### Sample Size

We assumed α=.05 (two-tailed; type I error rate) and β=.20 (type II error rate) for sample size estimation. The primary power analysis is based on virologic suppression (<200 copies per ml: yes or no) for TGD patients living with HIV (Tables 2 and 3). We hypothesize that medical gender affirmation (hormones and surgery vs none) will increase the proportion of HIV-infected TGD patients achieving viral suppression across follow-up. There is substantial variability in viral suppression rates among TGD people (eg, 50%-81%) [10-12,72,73]. A 25% increase in the proportion of TGD patients achieving viral suppression (moderate treatment effect), from 51% at baseline to 76% at follow-up, will require a minimum sample size of 182 patients living with HIV. Analyses of PrEP uptake and STI diagnoses are equally well-powered.

**Table 2 table2:** LEGACY cohort: parameter estimates used in sample size estimation for viral suppression, pre-exposure prophylaxis uptake, and sexually transmitted infection diagnosis.

Outcome variable		Parameter estimate
**Viral suppression**		
	P_0_^a^	0.51
	P_1_^b^	0.76
	Odds ratio^c^	3.04
	Risk ratio^d^	1.49
**PrEP^e^ uptake**		
	P_0_	0.011
	P_1_	0.048
	Odds ratio	4.53
	Risk ratio	4.36
**STI^f^ diagnosis**		
	P_0_	0.052
	P_1_	0.210
	Odds ratio	4.85
	Risk ratio	4.04

^a^P_0_: risk in group 0 (baseline risk).

^b^P_1_: risk in group 1 (exposed).

^c^Odds ratio: ((P_1_/(1-P_1_))/(P_0_/(1-P_0_)).

^d^Risk ratio: (P_1_ to P_0_).

^e^PrEP: pre-exposure prophylaxis.

^f^STI: sexually transmitted infection.

**Table 3 table3:** LEGACY cohort: sample size estimation for viral suppression, pre-exposure prophylaxis uptake, and sexually transmitted infection diagnosis.

Outcome variable			Outcome+		Outcome−		Total
**Viral suppression**							
	Group 1	113		36		149	
	Group 0	17		16		33	
	Total	130		52		182	
**PrEP^a^ uptake**							
	Group 1	49		967		1016	
	Group 0	2		221		223	
	Total	51		1188		1239	
**STI^b^ diagnosis**							
	Group 1	45		168		213	
	Group 0	2		45		47	
	Total	47		213		260	

^a^PrEP: pre-exposure prophylaxis.

^b^STI: sexually transmitted infection.

### Data Analysis

Descriptive statistics (eg, frequencies, means, and standard deviations) will be obtained to summarize the variables. Bivariate tests (*t* tests or *χ*^2^) will examine differences by site. Subsequent analyses will use appropriate statistical procedures to adjust for site differences if necessary. Bivariate tests (*t* tests or *χ*^2^) will examine medical gender affirmation by HIV outcomes of interest, followed by multivariable regression models. Analyses will use SAS software with two-tailed tests and an alpha .05-level of significance.

Aim 1 analyses will involve descriptive statistics to characterize medical gender affirmation exposures and HIV prevention continuum (HIVPC) and HIV care continuum (HIVCC) outcomes at baseline and each follow-up over 12 months. We will model longitudinal HIV-related outcome trajectories as a function of medical gender affirmation using generalized estimating equations [74]. Models will be adjusted for individual, interpersonal, and structural covariates and confounders. Moderators (eg, age, race, and gender identity) will be tested to identify TGD patients at the highest and lowest risk of adverse outcomes. For example, we will evaluate whether racial or ethnic self-identification (people of color vs White) is an effect modifier of hormones and viral suppression (ie, whether there is heterogeneity in treatment effects by race). Analyses will be appropriately stratified for heterogeneous treatment effects.

In aim 2, we will longitudinally model within-person changes in mental health diagnoses and response to standardized behavioral assessments from baseline (prehormones) to 12-months (aim 2) among TGD patients prospectively initiating hormone therapy at cohort entry. Mediational models will test whether changes in mental health explain the effect of medical gender affirmation on improved HIVPC or HIVCC outcomes.

Aim 3 analyses will entail descriptive statistics to characterize patient satisfaction with medical gender affirmation received, unmet needs and future desires for medical gender affirmation, and barriers and facilitators of medical gender affirmation.

Missing data can create significant problems in the analysis or interpretation of longitudinal data. Statistical summaries will be used to describe the missing data. We will assess patterns of missing data between or within follow-ups [75-77], comparing patients in care with those who drop out of care. We will use modern missing data techniques as appropriate, such as multiple imputation [78,79]. The impact of unmeasured confounders will be evaluated via sensitivity analyses [80]. We will also test for heterogeneity of treatment effects in medical gender affirmation and HIVPC or HVCC outcomes, consistent with the PCORI (Patient-Centered Outcomes Research Institute) methodology standards.

Fenway Health is the lead for data analysis and the creation of analytic data sets. This group is staffed by doctoral and master’s level biostatisticians who have extensive experience analyzing health outcomes using various statistical approaches. For LEGACY, they will be the primary resource for statistical consulting on any future grant proposals, concept sheets, study design, statistical analyses, and manuscript preparation. A delineated concept proposal process is in place to facilitate collaborations or data requests for the cohort. Any requests for access to the analysis data sets require previous approval from the principal investigator and applicable oversight bodies such as PCORI or the Fenway IRB.

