**Descriptive variables: HIVPC and HIVCC**								
	**HIV-infected patients**							
		Initiation of ART^j^ and adherence to ART	X		+		—	
		Retention in care	—		+		—	
		CD4 count	—		+		●	
		History of opportunistic infections	—		+		—	

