**Covariates and confounders: individual, interpersonal, and structural**								
	**Individual**							
		Demographics and TGD^k^ history	X		+		—	
		Mental health care and medication utilization	X		+		●	
		Substance use behavior or disorder	X		+		—	

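### The Aim 1 adjustment set contains no HIV-treatment or HIV-stage variable, so ART differences that predate hormone start can confound the viral-suppression comparison

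*Protocol article*

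**What the plan says.** Viral suppression in patients living with HIV is one of three primary outcomes and the one that sets the sample size: "The primary power analysis is based on virologic suppression" (Sample Size). The contrast is between exposure groups: "We hypothesize that medical gender affirmation (hormones and surgery vs none) will increase the proportion of HIV-infected TGD patients achieving viral suppression across follow-up".

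Table 1 sorts the study variables by role:

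- **Descriptive, patients living with HIV:** "Initiation of ART^j^ and adherence to ART", retention in care, CD4 count and history of opportunistic infections, all with the EHR as a source.
- **Covariates and confounders, individual:** demographics and TGD history, "Mental health care and medication utilization", and substance use.
- **Covariates and confounders, interpersonal:** transgender integration or adaptation, violence, and gender of partners.
- **Covariates and confounders, structural:** sex work, housing and incarceration, and stigma.
- **Mediators:** mental health diagnoses, distress and quality of life.

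The Aim 1 text then uses the same three covariate headings: "Models will be adjusted for individual, interpersonal, and structural covariates and confounders". The Limitations section acknowledges that patients select their own treatment. The planned sensitivity analysis for confounding concerns unmeasured confounders.

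**The concern.** ART is a direct determinant of viral suppression. A patient's ART status before starting hormones cannot be a result of the hormones, but it may be related to who starts them and when. It is therefore a candidate confounder of the main comparison, and the study measures it. As written, it enters neither the adjustment set nor the mediator list, and no restriction or stratification by ART is described. The sensitivity analysis for unmeasured confounders does not fill the gap, because ART is measured. The risk is that a difference in HIV treatment between the groups is reported as an effect of medical gender affirmation, or that such a difference hides a real effect.

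**Working it through.** **1. The plan's own figure.** The inputs are in Sample Size and Tables 2 and 3: "We assumed α=.05 (two-tailed; type I error rate) and β=.20 (type II error rate) for sample size estimation"; "from 51% at baseline to 76% at follow-up, will require a minimum sample size of 182 patients living with HIV"; and, for the exposed group (suppressed, not suppressed, total), "Group 1 113 36 149", against 33 unexposed.

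- Allocation ratio: k = 149/33 = 4.515.
- Pooled proportion: (0.51 + 4.515 × 0.76)/5.515 = 0.7147.
- Formula: n0 = [1.960 √((1 + 1/k) p̄(1 − p̄)) + 0.842 √(p0(1 − p0) + p1(1 − p1)/k)]² / (p1 − p0)²
- With numbers: (0.978 + 0.453)² / 0.0625 = 32.8, so 33 unexposed. Exposed: 33 × 4.515 = 149. Total 182, with power 80.2%.

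The 182 reproduces, so the sample size is not at fault. It is a crude comparison of two proportions between exposed and unexposed patients.

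**2. Roles compared.** Every row under the individual, interpersonal and structural headings was checked for an HIV-treatment or HIV-stage variable. There is none. The only row that mentions medication is worded for mental health care, and ART has its own row in the descriptive block.

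**3. What an imbalance would do.** The article gives neither ART prevalence by exposure group nor suppression on and off ART, so these are assumptions. With no true effect of exposure and ART prevalence a in a group:

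P(suppressed) = a × s_on + (1 − a) × s_off, so the false difference = (a1 − a0) × (s_on − s_off).

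With s_on = 0.85 and s_off = 0.15, the multiplier is 0.70:

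| ART, exposed vs unexposed | Suppression, exposed vs unexposed | False difference |
|---|---|---|
| 85% vs 75% | 74.5% vs 67.5% | +7 points |
| 85% vs 65% | 74.5% vs 60.5% | +14 points |
| 75% vs 85% | 67.5% vs 74.5% | −7 points |

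Over other assumed pairs (0.80/0.05, 0.85/0.10, 0.90/0.20), a 10-point imbalance gives 7 to 7.5 points. An imbalance of 33 to 36 points (0.25/0.75 to 0.25/0.70) would be needed to produce the whole planned 25-point difference.

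**4. Chance of a false finding.** For a crude two-proportion test over those three pairs, with 85% vs 75% on ART, the chance of a significant favourable result is about 14% to 16% at N = 182 and 25% to 28% at N = 421. With 85% vs 65% it is about 38% to 42% and 70% to 73%. These figures ignore the social covariates and repeated measures in the planned model, so they illustrate and do not forecast.

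**The case against.** **The table lists data sources, and the article is condensed.** Table 1 is titled as a list of sources, the Aim 1 sentence does not cite it or call the list closed, and a fuller plan could add covariates by outcome. That is fair as far as it goes. But the table also assigns roles, puts ART in a different role from the confounders, and shares its three headings with the adjustment sentence. The article states an assignment here; it is not merely silent.

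**ART may lie on the causal path.** The Conceptual Framework has affirmation increasing capacity to engage in HIV care, so adjusting for ART started or adhered to afterwards would remove part of the total effect. This stands and limits the point to values recorded before exposure.

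**Those values will often be unobservable.** Table 4 shows 6855 of 7821 patients (87.65%) with a current hormone prescription. That is the whole cohort, not only those living with HIV, but it suggests that many started before their record begins. This also stands. It argues against imputing pre-hormone values as routine and against treating cohort-entry ART as a clean baseline for everyone.

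**The comparison is not wholly unadjusted.** Social, behavioural and mental health covariates are in the models and may capture part of any ART difference. Outcomes are also modelled as trajectories, so stable differences would show in baseline suppression. Both soften the concern. Neither puts ART in the model.

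**Stronger readings.** A reader might infer that the bias favours the hypothesis, because patients settled in care may be likelier to have both ART and hormones. Nothing in the article supports that direction: patients long established on ART without hormones, compared with newcomers seeking hormones, would push the other way. A reader might also infer that ART differences could account for the whole planned effect. That needs an imbalance of a third or more between groups who are all recent primary care patients, and no figure in the article supports one.

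**Conclusion.** The point holds as a weakness in the stated analysis. A measured, strong determinant of the outcome that drives the sample size is given a descriptive role and left out of the named adjustment set, in a comparison where exposure is self-selected. Neither the size nor the direction of the bias can be identified from the document. The 7 points per 10-point imbalance rest on assumed suppression of 85% on ART and 15% off it, no true effect and no help from the other covariates. The point concerns pre-exposure HIV treatment and stage only; it is no argument for adjusting for ART that follows exposure. It deserves correction, but it does not show that the planned result would be wrong.

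**What to change.** For the viral-suppression model only:

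1. Add ART status, CD4 count and viral load from the EHR to the adjustment set, taken before hormone start or, for never-exposed patients, at cohort entry.
2. State that ART initiation and adherence after exposure are left out of the total-effect model, because the framework places engagement in care downstream.
3. Where hormones began before the available record, do not impute pre-hormone values as routine. Report the adjusted estimate in patients with an observed pre-exposure record. For prevalent users, show results with and without adjustment for cohort-entry ART as a sensitivity analysis, and note possible over-adjustment.

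The article already lists these items as EHR data, so no new collection is proposed. The cost is a few extra parameters and a smaller subset with observed pre-exposure values among about 421 patients living with HIV, so that estimate will be less precise. How large the subset is cannot be told from the article and should be counted before the analysis is fixed.
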